### Data analysis

2.2

Based on data from the currently recruited 550 patients, we found some incomplete ECG recordings of short duration, necessitating data analysis based solely on the ABP signal. To address this issue, we will conduct the eAD characterization on two fronts: one from both ECG and ABP waveforms, and the other from only ABP waveforms.

We will conduct non-invasive characterization of eAD by computing multiple indices over 24 h following admission, including heart rate turbulence (HRT) (18), time- and frequency-domain analyses of HRV and sequence analysis of BRS. First, we will slice the long-monitoring waveform into 1-h segments and assess the signal quality for both ECG and ABP segments. Next, the premature ventricular contractions (PVC) detection will analyze high-quality ECG segments. If more than 10 PVC beats for a given 1-h segment are detected, we will conduct HRT analysis on ECG waveforms (19). HRT is generally assessed by two parameters: turbulence onset (TO) and turbulence slope (TS). TO measures the initial acceleration and subsequent deceleration of heart rate after a PVC, while TS quantifies the rate of heart rate return to baseline. We will extract two time series from the ECG and ABP waveforms: one consisting of RR intervals from normal sinus beats, and the other comprising systolic blood pressures (sBP) from ABP pulses. We will then perform three analyses on these sequences: extracting root mean square of successive differences (RMSSD) and HRT from time-domain RR interval sequences, transforming RR intervals into the frequency domain to calculate the low- and high-frequency band ratio, and estimating BRS indices from RR intervals and sBP sequences. For eAD characterization based on ABP signals alone, we will compute autonomic indices from pulse interval sequences, excluding HRT due to the difficulty of detecting PVC beats without ECG waveforms. Figure 1 summarizes the entire procedure, with detailed explanations of each function block provided in the following sections.

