We will assess ABP signal quality using a singular value decomposition (SVD)-based approach (24). We will use our previously developed pulse detection algorithm to mark the onset of each ABP pulse, normalizing each pulse in both time and amplitude (25). Once the onsets of pulses are identified, we will adjust each pulse to a fixed length using spline resampling to ensure consistency in the number of data points across all pulses. Additionally, we will standardize each pulse’s amplitude by centering it around zero and scaling it to a standard deviation of one. Then, we will project this ABP pulse onto the signal subspace based on the SVD approach and calculate the signal-to-noise ratio. To obtain the signal and noise subspaces, we will implement SVD approach on an expert-validated reference library of 567 ABP pulses collected from 51 patients hospitalized at UCLA Ronald Reagan medical center. These valid ABP pulses will be subjected to the same normalization process. We will define the signal subspace and noise subspace after conducting SVD valid ABP pulses in the reference library. For a test ABP pulse, we will first project it onto the signal subspace and calculate the ratio of the energy of the projected signal over that of the projected noise. This ratio will be compared with a threshold, which is defined as the minimum calculated ratio among all the 567 pulses in the reference ABP library. This setting ensures that any ABP pulse closely resembling any pulse in the validated library is assessed correctly, providing a robust measure against false detections. The valid ABP pulses are those with calculated ratio greater than the threshold. We will conduct subsequent analysis only on the one-hour segments that pass both ECG and ABP signal quality assessments.

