#### Peaks detection

2.2.2

We will recognize R peaks for each ECG beat using a published QRS detection algorithm that includes four steps (26). The first step will use a sliding window of 2 s to capture the ECG signal. In the second step, we apply a band-pass filter ranging from 0.5 to 17 Hz to eliminate signal noise and motion artifacts. Then, we apply an enhancement mask to the filtered signal as Equation 4:

(4)
$$S\left(n\right)=\overset{k}{\underset{j=-k}{\sum }}M\left(k+j\right)E\left(n+j\right)$$

The enhancement mask 
M
 is defined as Equation 5:

(5)
$$\left\{\begin{array}{c} M\left(n\right)=-1,n\in \left[0,k-1\right]\\ M\left(n\right)=2*k,n=k\\ M\left(n\right)=-1,n\in \left[k+1,2k\right] \end{array}\right.$$

where 
E
 is the filtered ECG signal and 
S
 is the enhanced ECG signal. To eliminate variations in QRS amplitude, we will normalize the amplitude of the enhanced ECG signal to 1 using min-max normalization.

The third step is the detection of QRS fiducial points based on detected crests and troughs. Based on the normal range of the QRS complex in a typical lead-II ECG waveform, as shown in a published work, we will use a searching range of 0.3 s to detect the QRS complex. The searching process starts at the first point of the normalized ECG signal, and the amplitude threshold for detecting the QRS complex will be defined as 0.5 mV (26). The last step is the R peak recognition based on the detected QRS fiducial point. Since a normal QRS rangs is less than 0.12 s, the time interval for recognizing R peak is set as 0.24 s centering at the fiducial point in (26), and we identify the R peak successively.

For the high-quality ABP waveform, we will detect systolic blood pressure based on a published algorithm (27). Initially, we will apply a Savitzky–Golay filter to remove noise. Subsequently, we will utilize a sliding window to correctly identify the maximum point of the arterial pulse.

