#### BRS analysis

2.2.5

While heart rate changes due to acceleration and deceleration involve various physiological mechanisms beyond baroreceptor activity—including direct autonomic influences, mechanical factors, and other reflex pathways (37–39)**—**the combined analysis of baroreflex sensitivity (BRS) with directional heart rate changes offers a comprehensive view of autonomic regulation. This approach is particularly informative because the temporal relationship between blood pressure changes and subsequent heart rate responses helps distinguish baroreflex-mediated changes from other factors. Additionally, the magnitude and timing of these heart rate responses provide insights into baroreflex gain, even amid other regulatory influences. Analyzing both acceleration and deceleration also allows for the assessment of potential asymmetry in autonomic control, which is crucial in conditions like TBI where sympathetic and parasympathetic responses may be unevenly affected. By integrating these heart rate responses with traditional BRS measures, a more detailed understanding of cardiovascular regulation in sTBI patients is achieved, highlighting the complexities of impaired autonomic control.

We will use a phase-rectified signal averaging (PRSA) algorithm to compute BRS metrics. The process includes several steps regarding to the published paper (37):

Anchor points identification: if sBP values are higher than the preceding values, these values are defined as anchor points.For the synchronous RR intervals (RRI), each RRI is matched to a sBP value. A window length of 15-beat R-R intervals around each anchor point provides an optimal balance between capturing complete baroreflex responses and maintaining signal stationarity. Therefore, we select 15 RR intervals around each anchor point as a segment.Segments are aligned at the anchor points leading to a phase-rectification of the segments.Computation of PRSA signal: the PRSA signal 
$X\left(i\right)$
 is obtained by averaging the signals within the aligned segments, as shown in Equations 7, 8.

(7)
$$X\left(i\right)=\frac{1}{P}\overset{P}{\underset{p=1}{\sum }}RRI_{n_{p}}+l,\;l=-L,-L+1,\ldots ,L\text{.}$$

(8)
$$BRS=\frac{1}{4}\left[X\left(0\right)+X\left(1\right)-X\left(-1\right)-X\left(-2\right)\right]$$

where 
P
 is the total number of anchor points used in the averaging process. 
$RRI_{n_{p}}$
denotes the R-R interval values at the anchor point 
p
. 
$n_{p}$

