 is the index of the anchor points with the total number of 
P
. 
l
 is an index representing a range around the anchor points from 
−L
 to 
L
, where 
L
 is the length of the segments before and after the anchor point considered for averaging. The expression 
$RRI_{n_{p}}+l$
 indicates the RR interval value at the position offset by 
l
 from the 
$p^{th}$
anchor point. 
$X\left(0\right),X\left(1\right),X\left(-1\right)$
and 
$X\left(-2\right)$
are the PRSA signal values at offsets 0, 1, −1, and − 2, respectively.

In addition, we will estimate BRS in the frequency domain (27). We will identify an autoregressive with exogenous input (ARX) model with sBP time series as input and RR interval time series as output, which is indicated as Equation 9 (40):

(9)
$$RR\left(k\right)=\overset{N}{\underset{i=1}{\sum }}a_{i}*RR\left(k-i\right)+\overset{N}{\underset{j=0}{\sum }}b_{j}*sBP\left(k-j\right)+e\left(k\right)$$

where 
$a_{i}$
 and 
$b_{i}$
 are coefficients of the ARX model and 
e
 is a random error with zero mean. We will then calculate the PSD of the transfer function within the LF frequency band (0.04–0.15 Hz) and the gain of the transfer function will be used as an estimate of BRS as Equation 10 (41):

(10)
$$\alpha \left(LF\right)=\sqrt{\frac{P_{RR}\left(LF\right)}{P_{BP}\left(LF\right)}}\text{.}$$

where 
$P_{RR}\left(LF\right)$
 and 
$P_{BP}\left(LF\right)$
 indicate the spectral densities in LF band of RR interval and sBP time series, respectively.

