For the case of eAD characterization utilizing ABP signal alone, we will extract pulse-to-pulse interval (PPI) based on detected systolic blood pressure from high-quality ABP waveforms and calculate pulse rate variability. We identify the intervals between fiducial points in successive pulses as PPI. Based on PPI time series, we will calculate RMSSD, the ratio of LF/HF and BRS metrics in place of using RR interval time series.

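### Spectral BRS in the ECG + ABP branch takes RR intervals from sinus beats only but systolic pressures with no rhythm restriction, so alpha(LF) is biased down as PVCs become more frequent

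*Protocol article*

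**What the plan says.** Section 2.2 (Data analysis) defines two series for segments with both signals: "one consisting of RR intervals from normal sinus beats, and the other comprising systolic blood pressures (sBP) from ABP pulses". Both then go into "estimating BRS indices from RR intervals and sBP sequences".

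The sections that follow bear on which pressures enter:

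- **Signal quality assessment (2.2.1).** Each ABP pulse is resampled to a fixed length, centred and scaled to unit SD, then judged by a signal-to-noise ratio against a reference library. "The valid ABP pulses are those with calculated ratio greater than the threshold".
- **Peaks detection (2.2.2).** For systolic pressure, "we will utilize a sliding window to correctly identify the maximum point of the arterial pulse". There is no ectopy step.
- **PVC detection (2.2.3).** PVC locations are found, for the stated purpose of the HRT calculation.
- **BRS analysis (2.2.5), PRSA.** On anchors: "if sBP values are higher than the preceding values, these values are defined as anchor points". On pairing: "For the synchronous RR intervals (RRI), each RRI is matched to a sBP value".
- **BRS analysis (2.2.5), spectral.** Equation 9 is an ARX model of RR on sBP with a shared beat index k. Equation 10 gives alpha(LF) as the square root of P_RR(LF)/P_BP(LF), where the two terms "indicate the spectral densities in LF band of RR interval and sBP time series, respectively".
- **Heart/pulse rate variability analysis (2.2.6), ABP-only branch.** Pulse intervals replace RR intervals: "we will calculate RMSSD, the ratio of LF/HF and BRS metrics in place of using RR interval time series".

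Reduced BRS is one of the five eAD indicators. Three or more must lie beyond 2.5 SD of age- and sex-standardised values.

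**The concern.** A premature ventricular beat usually gives a weak arterial pulse, often followed by a stronger one after the pause. If those pulses stay in the sBP series while their intervals are taken out of the RR series, the ratio in Equation 10 compares two different sets of beats. The isolated pressure swings spread power across the spectrum, including 0.04-0.15 Hz, and only the denominator gains.

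The resulting error has a direction, towards low BRS, and a gradient, since it grows with the number of PVCs. Reduced BRS counts as abnormal, and the measures are also to be analysed as continuous variables against clinical outcomes. Frequent ectopy could then be read in part as a weak baroreflex. The ABP quality screen is not designed to prevent this. It scales amplitude away before testing shape, so a low pulse of ordinary shape passes.

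**Working it through.** The documents state no bias figure, so there is none to reproduce. The direction follows from the text; the size needs assumptions.

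**Direction.** Let S be the true LF power of sBP and A the LF power added by ectopic pulses. If the RR side is limited to sinus beats and the pressure side is not,

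alpha(observed)/alpha(true) = sqrt(S/(S + A)), which is below 1 whenever A > 0.

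**Inputs.**
- From the plan: LF band 0.04-0.15 Hz (width 0.11 Hz); 1-h segments; more than 10 PVCs per segment triggers HRT.
- Assumed: 80 beats/min, hence 4,800 beats/h at 0.75 s spacing and a Nyquist limit of 1/(2 × 0.75) = 0.667 Hz; PVC pulse 30 mmHg low; next pulse 5 mmHg high; S = 2 to 9 mmHg²; PVCs placed at random.

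**Added power.** One PVC contributes the squared response 30² + 5² − 2 × 30 × 5 × cos(2π × 0.75 f), which averages about 658 mmHg² over the LF band. With p the share of beats that are PVCs,

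A ≈ p(1 − p) × 658 × 0.11/0.667.

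| PVCs/h | p | A (mmHg²) | Ratio, S = 2 | Ratio, S = 9 | Fall in alpha(LF) |
|---|---|---|---|---|---|
| 11 | 0.23% | 0.25 | 0.94 | 0.99 | about 1-6% |
| 96 | 2% | 2.1 | 0.70 | 0.90 | about 10-30% |
| 240 | 5% | 5.2 | 0.53 | 0.80 | about 20-47% |

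For example, at 96/h with S = 2: sqrt(2/4.1) = 0.70. Simulated beat series give the same added power (0.25, 2.1 and 5.2 mmHg²).

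**Check with other assumptions.** A second simulation used a Lomb-Scargle spectrum, true gain 8 ms/mmHg, LF SD of sBP 1.5 or 2.5 mmHg, PVC pulse 20 or 40 mmHg low, and next pulse 5 or 10 mmHg high. The ratio of unmatched to matched alpha(LF) was 0.90-0.99 at 11/h, 0.68-0.94 at 60/h and 0.53-0.90 at about 240/h. With both series limited to the same sinus beats, alpha(LF) stayed at 8.0 at every PVC count, so the unequal beat sets are the cause.

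**PRSA.** Equation 8 contains RR terms only; pressure enters by choosing anchors. In the same simulation, PRSA BRS was at most 0.2% below its matched value at 11/h and about 2-5% below at about 240/h.

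**ABP-only branch.** Intervals and pressures come from the same pulses and neither side has a sinus restriction, so this mismatch does not arise.

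**Limits.** Neither simulation models heart rate turbulence after the PVC or the ARX fit.

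**The case against.** **The series may be paired in practice.** Section 2.2 is an overview. It speaks of ABP pulses, not of every pulse, and these pass a validity screen that may reject some PVC pulses by shape. The PRSA steps match each RR interval to a pressure, Equation 9 uses one beat index for both series, Figure 1 is not shown, and an article may leave ectopy editing to the full plan. This is fair, and the code may already do what is needed. But the article does state a beat restriction and puts it on one side only. The pairing rule appears under PRSA, not under Equation 10. A shared index k does not say which beats it counts.

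**The bias could go the other way.** If the long interval spanning a PVC were kept as a sinus RR interval, the numerator would be inflated. With a true gain of 8 ms/mmHg and an interval about 750 ms too long, alpha(LF) would be multiplied by 1.15-1.54 at 11/h and 2.3-3.1 at 240/h. The sinus-only wording does not naturally allow such intervals, and the same mask with a gap rule would remove this error too.

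**The effect is small at the one PVC count the plan names.** This stands. Just above 10 PVCs per hour the fall is 1-6%, or up to 10% in the second simulation. The larger figures need frequent ectopy, and the documents give no PVC rate for this population.

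**A stronger reading goes too far.** A reader might infer that PVC pulses depress BRS in general and create false findings of reduced BRS, or of eAD. The documents do not support that. PRSA, the estimator described first, is barely affected, and one biased index cannot meet a rule that needs three.

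**Conclusion.** The point holds for the spectral BRS in the ECG + ABP branch. Followed as written, the construction leaves PVC and post-PVC pulses in P_BP(LF) while the matching intervals are left out of P_RR(LF), so alpha(LF) is biased down increasingly with PVC count. The range runs from about 1-6% at 11 PVCs per hour to 20-47% at 240, and rests wholly on the assumed pulse depths, heart rate and LF power.

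A share of patients wrongly called low cannot be derived. It is tempting to treat 4.87-34.07 as a central 95% range and count values below 4.87, but section 3 gives that range as one across age groups and sets the cut-off at 2.5 SD, with neither SD nor scale stated. The answer depends on that reading. A log-normal with those values as 95% limits has its 2.5 SD cut-off near 3.72. The share below it would rise from 0.6% to about 0.7-0.9% at 11 PVCs/h, 1.1-3.9% at 96 and 2-11% at 240. On an untransformed normal scale the cut-off is about 0.85 and the worst case is 0.8%. These figures show the sensitivity to the reading and are not estimates.

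The matter should be settled before the BRS indices are computed, chiefly because the cure is cheap and specific.

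**What to change.** In section 2.2 and in the spectral part of section 2.2.5, state one common sinus-beat mask for RR and sBP:

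1. Use the PVC locations already detected to drop the PVC pulse and the first pulse after the pause from sBP, with the corresponding intervals dropped from RR, and keep RR-sBP pairs by beat.
2. State one gap rule for both estimators: no ARX lag, PRSA anchor (with its preceding beat) or PRSA window may cross a removed beat.
3. State that P_RR(LF) and P_BP(LF) in Equation 10 come from these paired series.

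The cost is a few lines of code and a small loss of beats and anchors around PVCs. If the code already works this way, one sentence saying so is enough.

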**Figure 1 fig1:**
[figure not shown]
Flow diagram to compute automatic indices from 1 h ECG and ABP segments.

#### Signal quality assessment

2.2.1

The collected waveforms may include uncontrollable noise from sensor circuits, body motion, and poor electrode attachment, making it nearly impossible to perform a reliable beat detection of such contaminated ECG and ABP waveforms. Therefore, it is essential to assess the signal quality to ensure that the eAD is characterized promisingly on high-quality waveforms.

We will assess ECG signal quality and select the lead with the best quality, based on our previous work (20). Comparable with the visual quality assessment of multi-lead ECG signals that clinicians traditionally use, we will plot collective multi-lead ECG signals in the standard paper-ECG format with grid marks and format as a multi-lead ECG image. Then, we will construct ECG image templates of two groups (good quality and poor quality) from the training database, which will be achieved by the agglomerative hierarchy cluster analysis (21) based on the structural similarity measure (SSIM).

Suppose we have a pair of ECG image 
$X={\left[x_{1}^{T},\ldots ,x_{M}^{T}\right]}^{T}$
 and 
$Y={\left[y_{1}^{T},\ldots ,y_{M}^{T}\right]}^{T}$
, where 
$x_{m},y_{m}\in R^{N}$
,
m=1,…,M
, and M is number of leads. The SSIM between two single lead ECG 
x
 and 
y
can be calculated as Equations 1, 2

(1)
$$\mathrm{SSIM}\left(x,y\right)=\frac{\left(2\mu_{x}\mu_{y}+C_{1}\right)\left(2\partial_{xy}+C_{2}\right)}{\left(\mu_{x}^{2}+\mu_{y}^{2}+C_{1}\right)\left(\partial_{x}^{2}+\partial_{y}^{2}+C_{2}\right)}$$

where

(2)
$$C_{1}={\left(K_{1}L\right)}^{2},C_{2}={\left(K_{2}L\right)}^{2},K_{1}<<1,K_{2}>>1$$

$\mu_{x},\mu_{y},\partial_{x},\partial_{y}$
 and 
${б}_{xy}$
are means, standard deviations and cross-covariance of 
x
 and 
y
. 
$C_{1}$
 and 
$C_{2}$
 are constants depending on the dynamic range of each ECG sample. For each ECG pair with 
M
 leads, we will have a total of 
M×M
 values and use the mean value as final similarity. All similarity values are divided into two groups using 2-means clustering, corresponding to good and bad quality, respectively. For an ECG image cluster containing a total of 
T
 images, the representative one with index 
c
 can be choose by Equation 3

(3)
$$\begin{array}{c} c=\underset{j\in \left[1,N\right]\;}{\mathrm{argmax}}\frac{\sum_{i=1}^{N}S\left(I_{i},I_{j}\right)}{N}\;\\ \;\;\;\; \end{array}$$

where 
N
 is the number of images in the cluster, and 
$S\left(I_{i},I_{j}\right)$
 is the SSIM result between the image 
$I_{i}$
 and 
$I_{j}$
 within each cluster. Lastly, we format the result of SSIM between each test ECG image and template images as the input features to the linear discriminant analysis classifier to determine ECG quality.

For multi-lead ECG recordings with good quality, we will further select the optimal ECG lead. We will calculate several signal quality indices (SQIs) for each lead from a good-quality recording as introduced in published works (22, 23): (1) the consensus beat detection signal quality index (bSQI), which measures the percentage of beats detected by two beat detection algorithms; (2) the spectral distribution SQI (sSQI), which calculates the proportion of the spectral distribution of a given ECG segment found to be within a certain physiological frequency band; (3) the kurtosis-based SQI (kSQI), which evaluates the kurtosis of a segment. Then, we will combine these individual SQIs into a composite signal quality index to select the optimal lead based on expert knowledge.

We will assess ABP signal quality using a singular value decomposition (SVD)-based approach (24). We will use our previously developed pulse detection algorithm to mark the onset of each ABP pulse, normalizing each pulse in both time and amplitude (25). Once the onsets of pulses are identified, we will adjust each pulse to a fixed length using spline resampling to ensure consistency in the number of data points across all pulses. Additionally, we will standardize each pulse’s amplitude by centering it around zero and scaling it to a standard deviation of one. Then, we will project this ABP pulse onto the signal subspace based on the SVD approach and calculate the signal-to-noise ratio. To obtain the signal and noise subspaces, we will implement SVD approach on an expert-validated reference library of 567 ABP pulses collected from 51 patients hospitalized at UCLA Ronald Reagan medical center. These valid ABP pulses will be subjected to the same normalization process. We will define the signal subspace and noise subspace after conducting SVD valid ABP pulses in the reference library. For a test ABP pulse, we will first project it onto the signal subspace and calculate the ratio of the energy of the projected signal over that of the projected noise. This ratio will be compared with a threshold, which is defined as the minimum calculated ratio among all the 567 pulses in the reference ABP library. This setting ensures that any ABP pulse closely resembling any pulse in the validated library is assessed correctly, providing a robust measure against false detections. The valid ABP pulses are those with calculated ratio greater than the threshold. We will conduct subsequent analysis only on the one-hour segments that pass both ECG and ABP signal quality assessments.

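### Equation 2 sets K2>>1, which compresses the structure term of SSIM to near 1, so small differences in lead mean swamp waveform shape in the ECG quality features

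*Protocol article*

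**What the plan says.** Section 2.2.1 (Signal quality assessment) defines SSIM in Equation 1 as the product of a mean term and a structure term. Its inputs "are means, standard deviations and cross-covariance of" the two traces. Equation 2 gives C1=(K1 L)² and C2=(K2 L)², with K1<<1 and K2>>1, and the text adds that C1 and C2 "are constants depending on the dynamic range of each ECG sample". No numeric K1, K2 or L is given, and nothing elsewhere in the article states a different condition on K2.

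SSIM is then used three times in that section:
- It is the similarity for the hierarchical clustering that builds the good- and poor-quality templates, and for choosing each cluster's representative image (Equation 3).
- It drives the split into good and bad: "All similarity values are divided into two groups using 2-means clustering, corresponding to good and bad quality, respectively".
- It supplies the classifier features: "we format the result of SSIM between each test ECG image and template images as the input features to the linear discriminant analysis classifier".

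The section closes with: "We will conduct subsequent analysis only on the one-hour segments that pass both ECG and ABP signal quality assessments".

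**The concern.** C1 and C2 are there to stabilise two ratios. A constant that is small against the signal does this without changing what the ratio measures; a constant much larger than the signal replaces it. With K2>>1, C2 dominates both the covariance in the numerator and the variances in the denominator of the structure term, and this is the only part of SSIM that compares waveform shape. C1 stays small, so the mean term keeps nearly its full range.

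At stake is the admission of ECG to the analysis. SSIM values are the only features named for the classifier that decides ECG quality, and the ECG-based RMSSD, LF/HF, HRT and BRS all lie downstream of it. If the printed setting were used, those features would carry almost no information on shape.

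**Working it through.** **Inputs.** From Section 2.2.1: Equation 1, and Equation 2 with K1<<1 and K2>>1. Assumed, because the article gives no values: K1=0.01; K2=3 to 100 for the printed condition and 0.03 for the corrected one; L taken as a range covering both traces.

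**Step 1. Split Equation 1.**
- Mean term: (2 μx μy + C1)/(μx² + μy² + C1)
- Structure term: (2 σxy + C2)/(σx² + σy² + C2)

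**Step 2. Bound the structure term.** A signal of range L has variance ≤ L²/4. Hence σx² + σy² ≤ L²/2 and 2σxy ≥ −L²/2. Dividing through by L², the lowest attainable value, reached by a perfectly inverted trace of maximal variance, is (K2² − 0.5)/(K2² + 0.5).

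| K2 | Calculation | Floor |
|---|---|---|
| 0.03 | (0.0009 − 0.5)/(0.0009 + 0.5) | −0.996 |
| 3 | 8.5/9.5 | 0.895 |
| 5 | 24.5/25.5 | 0.961 |
| 10 | 99.5/100.5 | 0.990 |
| 100 | 9999.5/10000.5 | 0.9999 |

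For two uncorrelated traces, each with SD 0.15 L, the term is K2²/(K2² + 2×0.15²): 0.995 at K2=3 and 0.9996 at K2=10, against 0.020 at K2=0.03.

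**Step 3. Range of the mean term.** Take K1=0.01 and one mean at 0.05 L. If the other mean is 0.05 L, 0.02 L, 0 or −0.05 L, the mean term is 1.00, 0.70, 0.04 or −0.96. Modest differences in mean therefore move SSIM far more than the structure term can at K2=10.

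**Step 4. Simulation.** There were 600 ten-second synthetic single-lead traces, compared with a clean template. Half were the template plus noise of SD 0.02, and half were pure noise of SD 0.3, in units of R-wave height. All were given the template's mean, and then a random offset was added. K1=0.01; L was the larger range of the pair. AUC is for SSIM separating clean from noise.

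| Offset SD (of R-wave height) | AUC, K2=0.03 | AUC, K2=10 | Rank correlation of SSIM with absolute offset, K2=10 |
|---|---|---|---|
| 0 | 1.00 | 1.00 | – |
| 0.02 | 1.00 | 0.52 | −0.99 |
| 0.05 | 0.93 | 0.52 | −0.95 |
| 0.1 | 0.77 | 0.51 | −0.88 |

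At K2=10 the structure term averaged 1.0000 for clean ECG and 0.9997 for noise. With any offset variation, the variance of the mean term was 1.0002 to 1.0003 times that of SSIM. K2=3 and K2=100 gave AUCs of 0.45 to 0.54 once offsets varied. A separate run with offsets of 0.02 to 0.1 mV gave 0.49 to 0.54 at K2=10, against 0.9999, 0.86 and 0.67 at K2=0.03.

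**Step 5. What does not depend on K2.** For a synthetic ECG with a 1 mV R wave and L=2 mV, shifting the same clean trace by 0.1 mV or 0.3 mV gives SSIM of about 0.73 or 0.39, both at K2=10 and at K2=0.03. The fall in the K2=0.03 column of Step 4 has the same source: the mean term.

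**The case against.** **It is probably a notation slip.** The same section prints sigma with inconsistent symbols and uses both T and N for the number of images in a cluster. The method is attributed to the authors' previous work, whose K1, K2, L and preprocessing are not visible here, so the code may well be right. This stands as a reason not to assert that the pipeline has failed. It does not remove the error in the formula as stated.

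**A reader might infer that SSIM then cannot tell a clean ECG from a flat line, noise or an inverted trace.** That is too strong. At K2=10 such traces score close to 1 only when their means match that of the clean ECG. At their own means, a flat line at 0 mV scores about 0.06 and a sign-inverted ECG about −0.93. When all means are equal, the score is compressed but still ordered by shape (AUC 1.00), and linear discriminant analysis is unaffected by linear rescaling of a feature. The loss of separation needs lead means to vary between recordings, which the article neither states nor excludes. The only ECG filter it describes comes later, in Section 2.2.2: "we apply a band-pass filter ranging from 0.5 to 17 Hz to eliminate signal noise and motion artifacts".

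**A reader might also infer that K2>>1 causes good ECG to be rejected for baseline shift.** It does not: Step 5 gives the same penalty at K2=0.03.

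**Other safeguards exist.** bSQI, sSQI and kSQI follow SSIM, and the Abstract describes quality assessment as a combination of the two. In Section 2.2.1, however, they only choose the best lead of a recording already classed as good and are not described as rejecting any. The ABP-only route avoids ECG altogether. Both mitigate in part.

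**SSIM may be computed on image pixels.** The mean term would then reflect image intensity and the millivolt figures would not carry over. The bound in Step 2 applies either way.

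**Conclusion.** The point holds as an error in a stated formula. Followed as printed, Equation 2 leaves the structure term with a floor of 0.961 at K2=5 and 0.990 at K2=10. Variation in lead mean of about 0.02 of R-wave height is then enough to bring separation of clean from noisy ECG down to chance.

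The bound is exact, provided that L covers both traces; it weakens if L comes from one trace and the other is much larger. The AUCs rest on assumed K1, K2, offsets and ECG shape. In the simulation clean traces were aligned in time with the template, so the K2=0.03 figures are a favourable case. The article does not show that bad ECG has been or will be admitted, since the coded setting is unknown. The correction should be made because this score is the only named basis for accepting ECG, and because it is cheap.

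**What to change.** 1. Change Equation 2 to K1<<1 and K2<<1, and state the values of K1 and K2 and how L is defined (per trace, per pair or fixed; voltage or pixel scale).
2. Confirm which setting was coded. If it was K2<<1, the text correction is all that is needed. If K2>>1 was used, re-run template construction, the 2-means split and the classifier.
3. As a separate and inexpensive improvement, remove each lead's mean before computing SSIM, unless the preprocessing in the earlier work already does so. This deals with sensitivity to baseline shift, which changing K2 does not.

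The cost is one symbol and a sentence of text, plus at most a re-run of an automated step. No new data are needed.
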